### Missing Data

Baseline variables used by the AFC tool are routinely collected in the electronic health record and are therefore expected to be minimally missing. For follow-up outcomes, mortality is centrally collected (and therefore not expected to yield missing data). However, intercenter variability in data capture may occur. Therefore, for time-to-event outcomes (survival), patients will be censored at the last known follow-up in accordance with standard survival analysis methods. For binary and continuous secondary outcomes (eg, antimicrobial resistance and antibiotic use), we will assume data are missing at random and apply multilevel multiple imputation, using Rubin rules. For the window-based prescribing outcomes, windows without in-hospital systemic antibiotic exposure are considered not applicable (“no opportunity”) rather than missing and are excluded from the denominator of the cumulative primary end point. Patients without any applicable windows (no in-hospital antibiotic exposure in any assessment window up to day 100) will be excluded from the primary end point analysis, as the cumulative guideline-concordance proportion is not defined for these patients. The number and proportion of such patients will be reported by study phase. The proportion and patterns of missing data will be reported accordingly, and sensitivity analyses will be conducted using complete-case analyses and worst-case assumptions to assess the robustness of findings.

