### Ethical Considerations

This clinical study was initiated after evaluation and approval by the Research Ethics Committee UZ/KU Leuven (S68439, protocol version 5, July 2, 2025), and after consultation with the ethics committees (EC) of each participating center in Belgium (Commissie voor Medische Ethiek [CME] Noorderhart [S504409]; EC St-Jozefskliniek Izegem [S504492]; CME Heilig Hart Ziekenhuis Mol [S504443]; CME AZ Herentals [S504441]; CME AZ Turnhout [S504448]; CME AZ Sint-Maria, CME RZ Tienen and CME AZ Voorkempen [approval granted; S-numbers pending]).

This study was classified as a noninterventional quality improvement project. The project does not introduce a new clinical treatment or experimental procedure but consists of systematically identifying discordances in existing electronic health records (ie, documented BLALs despite proven prior tolerance) and communicating this information to the treating physician through a decision-support process. The final clinical decision always remains with the treating physician and follows existing international and national guidelines. No additional diagnostic or monitoring procedures are imposed, and no automatic delabeling is performed by this study’s team. Therefore, this study does not mandate changes in patient management but supports standard-of-care decision-making. Under Article 2, §8 of the Belgian Law of 7 May 2004 [31], this project qualifies as a noninterventional study, as medications are prescribed according to routine clinical practice, no additional diagnostic or monitoring procedures are imposed, and epidemiological methods are used for analysis. Moreover, the risks for participants are minimal and proportionate to the anticipated benefits. However, for methodological clarity, the term “intervention” is used in this protocol but refers solely to an informational decision-support process and not to a patient-level clinical intervention.

Therefore, individual informed consent is not required. Instead, a structured patient notification and opt-out procedure is implemented in accordance with institutional policies[32].

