### Follow-Up or Outcome Measurement

To evaluate the effectiveness and safety of the intervention, information on antibiotic prescriptions, BLAL details, safety indicators, clinical outcomes, microbiological end points, and economic factors will be extracted from the EPR at days 30, 100, and 200. Antibiotic prescription will be monitored throughout the follow-up period. BLAL details will include the outcome of the assessment, along with any newly recorded or relabeled BLALs. The primary outcome is assessed per patient at the predefined time points. Inconclusive outcomes will be single-blinded evaluated by 2 independent infectious disease specialists who, upon disagreement, discuss the outcome with a third senior infectious disease specialist for a consensus. In the absence of doubt regarding the use (or not) of a first-line regimen, the scores are scored (unblinded) by the central study team (n=2). Safety parameters will be evaluated based on antibiotic tolerance and the need to switch antibiotics during treatment. Clinical outcomes will be assessed by measuring the number of days until in-hospital mortality, mortality at 3 months posthospitalization, LOS, and ICU admission rate. Microbiological end points will include colonization and/or infection of methicillin-resistant *Staphylococcus aureus*, vancomycin-resistant *Enterococcus*, and *C. diff.* economic end points, focusing on the societal perspective, will capture the cost of antibiotic treatment and hospitalization, as well as the time and human resources required. However, detailed economic analysis will be the subject of a separate protocol. No patients will be lost to follow-up within participating hospitals, as this study relies exclusively on back-office EPR data extraction. Outcomes are captured through the shared EPR platform “Clinical Workstation” (CWS, Nexuzhealth), a multihospital EPR network used by several tertiary and regional Belgian hospitals. However, antibiotic exposure and readmissions are only captured for hospitals using this EPR network; outpatient antibiotic use and care in nonnetwork hospitals are not captured. Moreover, survival is centrally registered and automatically linked to the patient’s Belgian social security number, allowing us to reliably follow up on this parameter irrespective of subsequent hospitalizations.

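### Missing-at-random imputation is a poor fit for the resistant-organism endpoints, because an absent MRSA, VRE or C. difficile result would mostly mean that routine care did no test

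*Protocol article*

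**What the plan says.** All references are to the protocol article.

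- **Missing Data** sets the rule: for binary and continuous "secondary outcomes (eg, antimicrobial resistance and antibiotic use), we will assume data are missing at random and apply multilevel multiple imputation", pooled by Rubin rules. Antimicrobial resistance is one of its two named examples. For robustness, "sensitivity analyses will be conducted using complete-case analyses and worst-case assumptions to assess the robustness of findings". The section does not define worst case.
- **Follow-Up or Outcome Measurement** sets the endpoint: "Microbiological end points will include colonization and/or infection of methicillin-resistant" S. aureus, VRE and C. difficile. On the data source, "this study relies exclusively on back-office EPR data extraction". On dropout, "No patients will be lost to follow-up within participating hospitals". On coverage, "outpatient antibiotic use and care in nonnetwork hospitals are not captured".
- **Ethical Considerations** states: "No additional diagnostic or monitoring procedures are imposed".
- **Missing Data** also separates absence from missingness for the prescribing windows: a window without in-hospital antibiotics counts as no opportunity and is not imputed. No matching rule is given for a patient without a microbiology test.

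**The concern.** A culture, screen or toxin test exists only where routine care ordered one. Orders usually follow symptoms, exposure or local screening policy, and each of these is related to the result. Missing at random would need an imputation model that captures the reason for testing. The article does not list the imputation variables. The covariates it names for the adjusted primary model (age, sex, Charlson index) would not do this.

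If untested patients enter the imputation as missing, they borrow the positivity of tested patients with similar covariates. The reported risk of a resistant organism then describes tested patients, not hospitalized patients with a beta-lactam allergy label. If testing intensity also differs between phases, the comparison mixes testing with occurrence. The two planned missing-data sensitivity analyses do not resolve this, and the covariance-structure and GEE checks under Statistical Analysis address a different question.

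**Working it through.** The plan states no figure to reproduce. The check has two parts: what a missing value is likely to mean, and what each planned analysis would then return.

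**1. What a missing value means.** Loss to follow-up inside participating hospitals is ruled out. The remaining sources are no test recorded, care outside the network, and differences between centers in data capture, which Missing Data mentions. With no study-mandated test, the first is the most plausible main source. This is an inference; the article does not say it.

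**2. Identities.** Let t be the share tested, p the positivity among tested patients and u the positivity among untested patients.

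- True risk = t·p + (1 − t)·u
- Complete-case = p
- Missing-at-random imputation ≈ p, given the covariates in the model
- Worst case, read as every untested patient positive = t·p + (1 − t)
- Recorded detection among all patients = t·p

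**3. Assumed inputs.** The documents give none of these rates. Ranges used: t = 10-40%, p = 5-10%, u = 0-1%.

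| t | p | u | True | Imputed or complete-case | Worst case | Detected |
|---|---|---|---|---|---|---|
| 10% | 5% | 0% | 0.5% | 5% | 90.5% | 0.5% |
| 10% | 10% | 0% | 1.0% | 10% | 91% | 1.0% |
| 20% | 10% | 0% | 2.0% | 10% | 82% | 2.0% |
| 20% | 10% | 1% | 2.8% | 10% | 82% | 2.0% |
| 40% | 5% | 1% | 2.6% | 5% | 62% | 2.0% |
| 40% | 10% | 1% | 4.6% | 10% | 64% | 4.0% |

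The overstatement runs from 5/2.6 = 1.9 times to 10/1.0 = 10 times.

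**4. Does a relevant covariate help?** Assume 10% of patients are in ICU, suspicion arises in 50% of ICU and 10% of other patients, carriage is 10% with suspicion and 0.5% without, and testing is 90% with suspicion and 3% without.

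- Suspicion overall: 0.1 × 0.5 + 0.9 × 0.1 = 14%.
- True risk: 0.14 × 0.10 + 0.86 × 0.005 = 1.8%.
- Tested: 0.14 × 0.9 + 0.86 × 0.03 = 15.2%.
- Detected: 0.14 × 0.9 × 0.10 + 0.86 × 0.03 × 0.005 = 1.3%.
- Complete-case: 0.01273/0.1518 = 8.4%.
- Imputation within ICU strata: 0.1 × (0.04508/0.465) + 0.9 × (0.00914/0.117) = 8.0%.
- Worst case: 0.0127 + 0.8482 = 86%.

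A simulation of 400,000 patients agrees (complete-case 8.5%, imputation 8.0%). Knowing ICU status removes little of the bias.

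**5. Phase comparison (control, then intervention).**

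- *Equal testing, 20% in both; all carriers tested; true 2.0% and 1.5%.* Imputed: 2.0/0.2 = 10% and 1.5/0.2 = 7.5%. The difference of −0.5 points becomes −2.5 points, while the risk ratio stays at 0.75. Worst case: 82% and 81.5%, so the difference is kept but the ratio shrinks to 0.99.
- *Unequal testing, 20% and 25%; all carriers tested; true 2% in both.* Imputed: 10% and 8%, a false difference of −2 points. Worst case: 82% and 77%, a false −5 points. Detected: 2% in both.
- *Positivity 10% in both; testing 20% and 15%.* Imputed: 10% in both. Detected: 2.0% and 1.5%, a difference made by testing alone.

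The last case shows that a detection endpoint also needs the testing rates beside it.

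**The case against.** The strongest reply is that the article never says an untested patient is coded as missing. It imputes data that are missing, and the cause it mentions is variation between centers in data capture. The endpoint could be a yes/no extraction in which no record means no event, and the bias would then not arise. This stands as a limit on certainty. It does not remove the point, because the text names antimicrobial resistance for imputation and gives no rule that keeps untested patients out.

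Other parts also stand:

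- A reader might infer that every test was done on suspicion. The article describes no testing practice at the hospitals, and routine screening at a site would shrink the bias there.
- A reader might infer that these endpoints will certainly be several times too high. Every rate used here is assumed, so no size can be asserted from the document.
- A reader might extend the point to antibiotic use, the other named example. For the window-based prescribing outcomes the no-opportunity rule already prevents imputation of absent records, so the document does not support that extension.
- A reader might infer that the problem would stay hidden. Missing Data promises the proportion and patterns of missing data, and a very large missing fraction would be partly revealing. It would not repair the estimate.
- Nothing in the article suggests that the tool changes microbiology testing.

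It may also be said that coding details belong in the analysis plan, which the article says will be finalized before database lock. That is true of the coding detail. The point here is the rule that the article does state, which a later plan would inherit.

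**Conclusion.** The point holds in a limited form, for the microbiological secondary endpoints only; the primary endpoint is untouched. The stated missing-at-random rule suits these outcomes badly, because an absent result is most plausibly an absent test. If untested patients are treated as missing, absolute risks and risk differences are overstated, by about 1.9 to 10 times for the risk over the assumed ranges. Complete-case analysis would appear to confirm the imputed result. Worst case moves the absolute risk further from the truth and distorts the comparison when testing differs.

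The conclusion rests on three assumptions: untested patients count as missing, testing is related to the outcome beyond the modeled covariates, and testing covers only a minority of patients. If testing is equal across phases, relative effects may be little affected.

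**What to change.** In the analysis plan, before database lock:

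- Define each microbiological endpoint as a recorded positive result in the network EPR up to the assessment day, among all included patients.
- Count a patient with no positive record as not detected, and do not impute untested patients.
- Restrict imputation to fields that should have been recorded but were not, such as data-capture failures at a center.
- Report testing rates by phase and period next to the endpoint, because detection depends on testing too.
- Show tested-only results as a sensitivity analysis.

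The cost is a few sentences, plus extraction of whether a test was done; no new procedures are needed. The downside is small: the endpoint becomes detected rather than true colonization or infection. It will miss carriers who were never tested (1.3% detected against 1.8% true in the ICU example) and positives found outside the network.

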### Sample Size Determination

The main aim of our study is to establish the assumed superiority of using the AFC over SOC in increasing the proportion of patients with first-line antibiotics prescribed. Therefore, we look at the proportion of patients receiving first-line or narrow-spectrum beta-lactam antibiotics within the total number of patients receiving antibiotics. The crossover design accounts for seasonal as well as intra- and interhospital differences in overall antibiotic use. Nevertheless, overall antibiotic use will be monitored at the participating sites during this trial’s period.

The following assumptions were applied.

For the control arm, in a recent retrospective study in UZ Leuven, involving 21,999 patients with pneumonia, pyelonephritis, infections associated with heart, kidney, liver, or lung transplantation; appendectomy; coronary artery bypass grafting; and total knee or hip replacement, we investigated the difference in antibiotic use between patients with and without BLAL [21]. It showed that 10.5% of patients with a BLAL received amoxicillin despite their label. Based on the latter, we estimate that 10% of the patients in the control group already receive first-line antibiotics. We add a 5% increase due to indirect learning of our protocol because we cannot exclude that treating physicians learn to use discordances in the medical file for delabeling or refinement of the allergy labels, independent of our study and AFC tool. Considering around 30% of hospitalized patients receive antibiotics during their stay [34], this brings the percentage down to 4.6% in the control group.

For the intervention arm, we previously showed that our CDS approach has the potential to delabel 38% of BLALs [30]. We add a margin of 5% for physicians or patients who refuse to delabel or be delabeled [9]. Considering around 30% of hospitalized patients will receive antibiotics during their stay, this results in an overall estimate for the intervention group of 9.9%.

For the intra- and intercluster correlation (ICC), literature indicates a moderate ICC of 0.059 for antibiotic prescription behavior [35,36]. This estimate seems appropriate as moderate differences in antibiotic prescription behavior are expected within and between different physicians at participating sites, which mostly follow the IGGI guidelines, however, with some internal adjustments. Indeed, the most recent point prevalence survey of antimicrobial use and health care–associated infections in Belgian acute care hospitals (results of the global point prevalence survey and European Center for Disease Prevention and Control point prevalence survey) reports 77% compliance with IGGI guidelines [37]. Additionally, 3 participating sites are part of the same Hospital Outbreak Support Team network, that is, Heilig Hartziekenhuis Mol, AZ Turnhout, and AZ Herentals in the Hospital Outbreak Support Team Network Kempen, which has the specific goal to align antimicrobial stewardship. All centers use the same EPR (CWS). The major difference would be expected between UZ Leuven, as an academic hospital, and the other participating sites, as regional hospitals. The AFC is currently only available in the CWS EPR system, and therefore, we were unable to include other academic centers as well. A sensitivity analysis of academic vs regional hospitals will be performed.

Considering the number of hospitalizations per year in each center and a prevalence of 6% of BLALs [8], we expect an inclusion rate of 3285 participants.

Sample size and power calculations were carried out according to the methods described by Hemming et al [38], using the Shiny CRT Calculator [39]. Based on the design given in Figure 1, assuming a discrete time decay (allowing correlations between periods to decay with each period), a within-period ICC of 0.059 and an autocorrelation (ratio of between-period and within-period ICC) of 0.6, this study will have 80% power to detect a statistically significant difference between control and intervention using a 2-sided significance level of 5%, assuming 4.6% and 9.9% of patients to have the primary end point in the control and intervention group, respectively. This sample size calculation is based on patient-level appropriate prescribing proportions and is considered a conservative approximation for the cumulative window-based primary end point.

In case key assumptions differ importantly from those used in the initial calculations, we will implement a preplanned sensitivity and adaptation strategy focused on nuisance parameters rather than treatment effect estimates. Once the initial target number of inclusions has been reached, we will conduct a blinded (or arm-masked) internal review of (1) overall primary end point incidence, (2) observed within-period ICC and between-period correlation structure, and (3) completeness of follow-up and outcome ascertainment across centers and periods. In parallel, we will run sensitivity power analyses across plausible ranges of ICC or autocorrelation to quantify the robustness of power under departures from assumptions. If this review indicates that statistical power is likely to be compromised (eg, lower-than-expected event rate or higher-than-expected clustering), we will adapt by extending recruitment and/or adding additional crossover periods and/or centers, while keeping the intervention allocation scheme and primary outcome definition unchanged, depending on the available human resources to perform this. Any such modifications will be documented as protocol amendments and reflected in an updated statistical analysis plan. Importantly, to avoid operational recruitment gaps and preserve feasibility, recruitment will continue while this internal review is performed, and the adaptation decision will be based on updated nuisance-parameter estimates rather than interim efficacy signals.

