### Statistical Analysis

The primary endpoint is cumulative guideline-concordant use of first-line and/or narrow-spectrum beta-lactam antibiotics according to IGGI-based local guidelines, assessed across predefined assessment windows up to day 100 (days 1, 30, and 100). Within each window, guideline concordance is scored at the patient level in an any or ever manner as 1 if at least one in-hospital systemic antibiotic course is guideline-concordant and 0 if otherwise. If multiple courses occur within a window, the window is considered concordant if any course meets guideline criteria. This any or ever approach was chosen in line with the quality-improvement objective of the AFC intervention, capturing whether appropriate first-line therapy was achieved within a care window while limiting instability due to multiple within-episode treatment changes. Windows without in-hospital systemic antibiotic administration are considered not applicable (“no opportunity”) and are excluded from the denominator.

For each patient, a cumulative weighted guideline-concordance score is calculated at day 100 as the proportion of applicable windows with guideline-concordant therapy (*sᵢ/nᵢ*). The primary comparison between intervention (AFC) and control will use a binomial generalized linear mixed-effects model with logit link, modeling *sᵢ* out of *nᵢ*, including fixed effects for study phase and period, and a random intercept for hospital to account for clustering in the crossover design. A prespecified adjusted model will additionally include age, sex, and the Charlson comorbidity index. Patients without any applicable windows will be excluded from this analysis and reported separately. The primary estimand targets the period during which the AFC is expected to plausibly influence prescribing through contemporaneous decision support and short-term label adjustment.

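### The two planning rates are measured differently (amoxicillin receipt against delabeling yield) and neither is the rate of the primary endpoint, so the 5.3-point difference and 80% power lack a common basis

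*Protocol article*

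**What the plan says.** Under Sample Size Determination, the control rate starts from a retrospective cohort at the university hospital: "It showed that 10.5% of patients with a BLAL received amoxicillin despite their label". The text continues: "Based on the latter, we estimate that 10% of the patients in the control group already receive first-line antibiotics". It then says "We add a 5% increase due to indirect learning of our protocol" and applies the share of inpatients who receive antibiotics, about 30%: "this brings the percentage down to 4.6% in the control group".

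The intervention rate has another source: "we previously showed that our CDS approach has the potential to delabel 38% of BLALs". Five points come off for refusal, and the same 30% gives 9.9%.

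The power statement in that section uses 4.6% and 9.9% as the shares of patients with the primary endpoint. Statistical Analysis defines the endpoint more broadly: "The primary endpoint is cumulative guideline-concordant use of first-line and/or narrow-spectrum beta-lactam antibiotics according to IGGI-based local guidelines". It is scored on an any-or-ever basis in windows up to day 100, and patients without in-hospital antibiotics are left out of the analysis.

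**The concern.** For a binary endpoint, the control proportion sets both the variance and the level from which improvement is measured. Here it is receipt of a single drug. A labelled control patient given a different guideline-concordant first-line beta-lactam is a success in the trial but is not in the 10.5%. Nothing in the article limits the endpoint to amoxicillin or adds the other qualifying drugs to the control figure.

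The intervention figure is not a prescribing rate at all. It treats every delabeled antibiotic recipient as a success and every other recipient as a failure, although the control arm is credited with some first-line use despite the label. The planned difference is therefore a delabeling share minus an amoxicillin share. What is at stake is whether the 80% power describes the comparison that will be made.

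**Working it through.** **1. The plan's rates.**
- Control: (10% + 5%) × 0.30 = 4.5%, or (10.5% + 5%) × 0.30 = 4.65%. The printed 4.6% follows from the amoxicillin figure up to rounding.
- Intervention: (38% − 5%) × 0.30 = 9.9%.
- Difference: 9.9 − 4.6 = 5.3 points.

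**2. The plan's power.** Inputs from the protocol: 3285 patients, nine hospitals, the four listed sequences, within-period ICC 0.059, autocorrelation 0.6 with discrete-time decay, two-sided 5%. Assumed: equal cluster-period sizes and the number of passes through the four-period sequence, because Figure 1 is not shown.

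The method is generalized least squares on cluster-period means with fixed period effects. The covariance between periods t and u is σ² × 0.059 × 0.6^|t−u|, with σ²(1 − 0.059)/m added on the diagonal. Here σ² = p̄(1 − p̄), p̄ is the mean of the two rates, and power = Φ(|difference|/SE − 1.96).

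At 4.6% against 9.9% the result is 54%, 84%, 93% and 97% for one, two, three and four passes. With two passes, m = 3285/(9 × 4) = 91.25, SE = 1.80 points, and 5.3/1.80 − 1.96 gives 84%. The stated 80% is attainable but cannot be confirmed. Two passes are used below.

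**3. One definition in both arms.** Let c be the endpoint rate among antibiotic recipients in the control arm; the plan's implied value is 10% + 5% = 15%. Assume that 33% are delabeled and that 77% of those then receive first-line treatment. The 77% borrows the guideline compliance that the protocol cites from a Belgian survey. The intervention rate among recipients is then 0.33 × 0.77 + 0.67c = 0.2541 + 0.67c. Multiplying both rates by 0.30 gives the plan's all-patient scale. The recipients-only scale uses 0.30 × 3285 ≈ 986 patients, so m = 986/36 ≈ 27.4.

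| c | Intervention, recipients | All-patient rates | Difference / SE (points) | Power, N = 3285 | Recipients: difference / SE (points) | Power, N ≈ 986 |
|---|---|---|---|---|---|---|
| 15% | 35.5% | 4.5% vs 10.6% | 6.14 / 1.84 | 92% | 20.5 / 3.79 | >99% |
| 20% | 38.8% | 6.0% vs 11.6% | 5.64 / 1.97 | 82% | 18.8 / 3.97 | >99% |
| 25% | 42.2% | 7.5% vs 12.6% | 5.15 / 2.09 | 69% | 17.2 / 4.12 | 99% |
| 30% | 45.5% | 9.0% vs 13.7% | 4.65 / 2.20 | 56% | 15.5 / 4.23 | 96% |
| 40% | 52.2% | 12.0% vs 15.7% | 3.66 / 2.40 | 33% | 12.2 / 4.35 | 80% |

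**4. Intervention rate left at the plan's 33% of recipients** (N ≈ 986). At c = 20% the difference is 13 points, SE 3.85, power 92%. At c = 25% it is 8 points, SE 3.96, power 52%.

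The answer thus depends on c, on whether the intervention rate moves with c, and on the population.

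**The case against.** The strongest reply is that no shortfall has been shown, and much of it stands.

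- **The two errors offset each other.** The 33% gives no baseline first-line use to the 67% not delabeled, so the intervention rate may be too low as well. At the planned c = 15%, one definition in both arms gives 92%, above the stated 80%. The intervention rate also leaves out refined labels, which the Introduction puts at a further 27%.
- **The analysed population is antibiotic recipients.** Under the 77% rule, power there holds up over the whole range from 15% to 30%.
- **Understatement is likely, not proven.** Amoxicillin receipt was not tested for guideline concordance, so some of the 10.5% could fail the endpoint. It is not a strict subset.

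A reader might infer that the trial is underpowered; the three points above show why the documents do not support that. A reader might also infer that the internal review would react only to a low event rate, since the text names "lower-than-expected event rate or higher-than-expected clustering". Those words are given only as examples. The trigger is power likely to be compromised, and overall incidence is reviewed without a stated direction.

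What does not stand is an appeal to the protocol's remark that its calculation is conservative. That remark concerns patient-level against window-based scoring, not which drugs count or how the two arms are measured. Nor does the internal review settle the matter: a pooled rate does not reveal the gap between arms, and the sensitivity power analyses as described vary only ICC and autocorrelation.

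**Conclusion.** The point holds as a mismatch of measures. The 4.6% derives from receipt of one drug, the 9.9% is a delabeling yield, and the power statement presents both as rates of the primary endpoint. The 5.3-point difference and the 80% power therefore have no common basis.

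The control rate is probably understated, by an amount the documents do not give. The net error in power could go either way. Over c = 15% to 30%, power runs from 92% down to 56% on the plan's all-patient scale and stays at 96% or more among recipients. It falls to 52% at c = 25% among recipients if the intervention rate is held at 33%. These figures rest on two passes of the sequences, equal cluster-period sizes, the stated correlations and, except in the fixed-33% case, 77% first-line use once delabeled. The endpoint definition and the planned analysis model are not affected.

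**What to change.** In Sample Size Determination, put both planning rates on the endpoint's measure:
- **Control rate:** the share of labelled, antibiotic-treated patients who receive any first-line or narrow-spectrum beta-lactam. Take it from the earlier cohort if that can be tabulated this way. The article does not say the cohort was coded for guideline concordance, so otherwise give a stated range.
- **Intervention rate:** (delabeled share × first-line use once delabeled) + (remaining share × control rate).
- **Power:** restate the detectable difference and the power from these two rates.

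In the internal-review paragraph of the same section, extend the sensitivity power analyses to a range of control rates. State also that a pooled incidence clearly above or below plan prompts recalculation. Results places that review in the month after March 2026, so the work can be done with it.

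The cost is a small rerun. The stated power may change in either direction. No extra patients are needed for this correction.
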